### Study design

This randomized trial will use an implementation hybrid design to assess the effectiveness and implementation parameters of IPT + TAU versus TAU alone for the treatment of PTSD and MDD among HIV+ GBV+ women served by the FACES clinic. IPT will be provided by non-specialists trained to deliver IPT in the HIV clinic setting. The TAU group will be offered IPT treatment following the initial 12-week trial. Thus, all study subjects will receive TAU throughout the study and they will all receive IPT in either the first or second half of the study. Study outcomes will be assessed at baseline, and weeks 12, 24 and 36 by a study evaluator who is blind to group assignment. The study protocol is approved by the UCSF Committee on Human Research and the KEMRI Scientific Ethical Review Unit.

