### Sample size

As an effectiveness-implementation hybrid type I, the primary goal of this study is to assess effectiveness, while also collecting data on implementation parameters [5]. In our prior work using a similar treatment with a traumatized, low-resource population, we observed a Cohen’s *d* effect size of 0.79 for depression symptoms [20]. Using the depression Cohen’s *d* would suggest that a sample size of at least 50 is necessary for a two-group design with power of 50 and probability level of 0.05. However, given cultural differences between studies, and that this study requires participants to complete four assessments across 36 weeks, with substantial time investment at each assessment, we have made a conservative sample size estimate, allowing for approximately 20 % general attrition at each assessment point, a sample size of 100 was selected. Given the multiple blood draws required of participants and the evidence suggesting that fear of blood draw can lead to attrition [50], we will further increase our sample size to 200 patients.

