### Statistical analysis

#### Effectiveness

The main analysis will consist of comparing the change from baseline to post-treatment (12 weeks) between the two treatment conditions. The two primary outcome measures of PTSD and MDD diagnosis will be analyzed by estimating and testing a statistical model of each dichotomous measure with a binomial distribution and log link using generalized estimating equations to account for clustering of participants by therapist (therapist effect) and the repeated assessments. Maintenance of gains will be assessed by testing for significant change from 12-week to 24- and 36-week follow-up assessments within each condition using McNemar’s test and repeated measures *t* tests.

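### The paired tests for maintenance of gains use only women seen at both visits, so the result may be overstated if relapse drives dropout, and loss of pairs lowers the power to detect lost gains

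*Protocol article*

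**What the plan says.** All statements are from the protocol article.

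- **Statistical analysis, Effectiveness.** The primary MDD and PTSD diagnoses are compared between arms from baseline to week 12 with generalized estimating equations (GEE). Maintenance is a separate, within-arm question, assessed by "testing for significant change from 12-week to 24- and 36-week follow-up assessments within each condition using" McNemar's "test and repeated measures" *t* tests.
- **Study design.** "Study outcomes will be assessed at baseline, and weeks 12, 24 and 36". Two of the three follow-ups therefore come after week 12.
- **Sample size.** The count starts from a statement that "a sample size of at least 50 is necessary for a two-group design". Then, "allowing for approximately 20 % general attrition at each assessment point", "a sample size of 100 was selected". Finally, because of the blood draws, "we will further increase our sample size to 200 patients".
- **Feasibility.** The statistical analysis section sets a benchmark of fewer than 50 women lost of 200. The implementation outcomes section sets 50 or fewer, with a target of 220.
- **Assessments.** The MINI, BDI and PCL-C are given to both arms at every visit.

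**The concern.** McNemar's test counts women whose diagnosis changed between two visits, and the paired t test averages within-woman differences. A woman without the later visit contributes to neither. Her week-12 scores are on file, and possibly her week-24 diagnosis, but the week 12 to 36 test cannot use them.

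Two things are at stake:

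1. **The estimate.** If return of depression or PTSD makes a woman less likely to attend, relapse among retained women is lower than relapse among all women seen at week 12, and the gains look more durable than they are.
2. **The decision.** Maintenance is judged by whether change is significant. A non-significant result is easily read as gains held, and fewer pairs make non-significance more likely even if dropout is unrelated to relapse.

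**Working it through.** **Step 1: reproduce the article's attrition arithmetic.** Inputs from the Sample size section: 50 women before attrition, 20% loss at each assessment, three follow-ups. 50 / 0.8³ = 97.7, against the stated 100. One step (50 / 0.8 = 62.5) or two (50 / 0.8² = 78.1) does not give 100. The allowance is therefore most naturally read as compounding over three follow-ups.

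**Step 2: loss between weeks 12 and 36.**

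| Basis in the article | Retained per visit | Week 12, per arm | Week 36, per arm | Lost, week 12 to 36 |
|---|---|---|---|---|
| Sizing allowance, 20% per assessment, 200 women | 0.80 | 80 | 51 | 1 − 0.8² = 36% |
| Feasibility limit, at most 49 of 200 lost, spread evenly | (151/200)^(1/3) = 0.911 | 91 | 76 | 1 − (151/200)^(2/3) = 17% |

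The other feasibility statement gives nearly the same: 1 − (170/220)^(2/3) = 16%. The even spread is an assumption. Under the limit of 49 of 200, the loss after week 12 could be anywhere from none to 49/200 = 24.5%.

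**Step 3: direction and size of bias.** Let f be the share lost. Relapse among all week-12 remitters = (1 − f) × relapse in retained + f × relapse in lost. The relapse rates are assumptions; the article gives none. With 10% relapse in retained women:

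| Relapse in lost women | All women, f = 17% | All women, f = 36% |
|---|---|---|
| 0% | 8.3% | 6.4% |
| 10% | 10.0% | 10.0% |
| 30% | 13.4% | 17.2% |
| 50% | 16.8% | 24.4% |

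The bias is zero when the two rates are equal and changes sign when lost women relapse less.

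The same check, starting from an assumed true relapse q = 30%: observed relapse = q·r₁ / (q·r₁ + (1 − q)·r₀), where r₁ and r₀ are retention in relapsed and non-relapsed women.

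- Overall retention 64%, r₁ = 0.50, r₀ = 0.70: 0.15 / (0.15 + 0.49) = 23.4%, which is 6.6 points too low. If 60% of 80 women had remitted (48), 64% of them is 30.7 women and the SE is √(0.234 × 0.766 / 30.7) = 7.6 points, so the bias is about 0.9 SE.
- The same retention with a gap of 10 or 30 points: 26.7% or 20.2%.
- Overall retention 82.9%, gap 20 points (r₁ = 0.689, r₀ = 0.889): 24.9%, which is 5.1 points too low.

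**Step 4: power.** Exact two-sided McNemar test at 0.05, assuming 18% of women relapse and 6% newly remit.

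| Basis | All week-12 women | Complete pairs, loss unrelated to relapse | Complete pairs, relapsed women 20 points less often retained |
|---|---|---|---|
| 36% lost | 53% (80) | 32% (51) | 12% |
| 17% lost | 59% (91) | 50% (76) | 27% |

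**The case against.** A reader might infer that maintenance *is* overstated and that the plan expects to lose 36% of week-12 attenders. The article supports neither.

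- **Direction is conditional.** Upward bias needs more relapse among lost women. The article attributes attrition to time burden and fear of blood draws, not to relapse. Relapse-driven dropout is plausible but is not the article's claim. This stands, and the point is worded accordingly.
- **36% is the upper figure.** It comes from an allowance the article calls conservative. Compounded, it means 200 − 102 = 98 women lost, about twice the feasibility limit. This stands, so the range of 17% to 36% is given. The problem shrinks at the lower end but does not vanish.
- **Missing-data handling belongs in the analysis plan, which is not shown.** This is right as far as it goes. The absence of imputation or sensitivity analyses from the article is not the fault raised. The fault is that the article names, as its maintenance analysis, tests that use complete pairs.
- **Power is already low with no dropout.** Also right: 53% with all 80 women under the assumptions above. That shows that a significance test is a weak basis for claiming maintenance at any level of loss. Losing pairs makes it weaker.
- **Standard models do not cure relapse-driven loss.** They assume that missingness depends only on observed data. This stands, so a sensitivity analysis is part of the fix.

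**Conclusion.** The concern holds in conditional form. The named tests discard every woman without the later visit, and the article's own figures put that at about 17% to 36% of week-12 attenders by week 36. Whether maintenance is overstated depends on relapse among the women lost, which the article does not give. Under the assumed 30% true relapse and a 20-point retention gap, the understatement of relapse is about 5 to 7 points. The loss of power does not depend on how lost women fare: on the assumed rates it falls from 59% to 50% at the smaller loss and from 53% to 32% at the larger. This matters because maintenance is read from a test for change.

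This is a secondary analysis, and the primary week-12 comparison is not affected. The reasoning applies to the IPT + TAU arm. The TAU arm is offered IPT after week 12, so its later change is not maintenance in the same sense; that is a separate matter.

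**What to change.** Replace the paired tests with models over weeks 12, 24 and 36 that include every woman with a week-12 assessment:

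- **BDI and PCL-C scores:** a likelihood-based mixed model for repeated measures.
- **MDD and PTSD diagnosis:** a mixed logistic model, or GEE after multiple imputation with earlier BDI, PCL-C and diagnosis as predictors. GEE without imputation or weighting is itself sensitive to informative loss.
- **Reporting:** give the change from week 12 with a 95% confidence interval, so that maintenance is not inferred from non-significance.
- **Sensitivity:** because these models assume data missing at random, vary the relapse rate in lost women over a stated range. Treat all lost women as relapsed only as the extreme bound. In the 36% example above it gives 0.64 × 23.4% + 36% = 51%, against an assumed truth of 30%, so it is not an estimate.

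The cost is analysis-plan wording and modest programming, with no new data. The analysis is slightly more complex, and the maintenance figure may be less favourable.

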**Methods/Design:**

In this effectiveness-implementation hybrid type I design, 200 HIV+ women with major depressive disorder (MDD) and posttraumatic stress disorder (PTSD) who are receiving care at a Family AIDS Care Education and Services (FACES)-supported clinic in Kisumu, Kenya will be randomized to: (1) interpersonal psychotherapy (IPT) + treatment as usual (TAU) or (2) TAU, both delivered within the HIV clinic. IPT will consist of 12 weekly 60-minute individual IPT sessions, delivered by non-specialists trained to provide IPT. Primary effectiveness outcomes will include MDD and PTSD diagnosis on the Mini International Diagnostic Interview (MINI). Primary implementation outcomes will include treatment cost-benefit, acceptability, appropriateness, feasibility and fidelity of the IPT delivery within an HIV clinic.

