#### Treatment as usual

At the FACES clinic, TAU resources for HIV+ GBV+ women include medical professionals, community elders, informal counseling, HIV treatment adherence counseling, church leaders, police, and pro-bono legal aid. These providers and services are available for access as needed. No explicit, evidence-based mental health treatment is currently available through TAU, although the social support implicit in each service is known to benefit mental health [25]. At week 12, TAU participants will complete their second assessment and will then be offered the same IPT treatment received by participants in the IPV + TAU arm. Thus, all study subjects will receive IPT during the course of the study.

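### In the TAU arm, maintenance of gains is tested from a pre-IPT visit, so the secondary analysis measures response to deferred IPT and leaves that arm's post-IPT interval untested

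*Protocol article*

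**What the plan says.** The protocol article's Statistical analysis section (Effectiveness) makes the between-arm comparison of change from baseline to week 12 the main analysis. It then adds one durability analysis: "Maintenance of gains will be assessed by testing for significant change". The rule is "testing for significant change from 12-week to 24- and 36-week follow-up assessments within each condition", so the contrasts run from week 12 to week 24 and from week 12 to week 36, and they are made "within each condition using McNemar’s test and repeated measures" t tests. The same reference visit and the same two contrasts therefore apply to both arms.

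The timing of treatment is given elsewhere:

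- Study design: "The TAU group will be offered IPT treatment following the initial 12-week trial", and "they will all receive IPT in either the first or second half of the study".
- Treatment as usual: "At week 12, TAU participants will complete their second assessment and will then be offered the same IPT treatment".
- Abstract, Methods/Design: "IPT will consist of 12 weekly 60-minute individual IPT sessions".
- Study design, on visits: "Study outcomes will be assessed at baseline, and weeks 12, 24 and 36".

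The article gives no separate maintenance contrast for the arm that receives IPT later.

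**The concern.** A maintenance test needs a reference visit at the end of treatment. Week 12 is that visit in the IPT + TAU arm. In the TAU arm it is the last visit before IPT is offered.

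One label then covers two different quantities. In the IPT + TAU arm, absence of significant worsening after week 12 supports durability. In the TAU arm, effective IPT produces a significant change after week 12, in an analysis meant to show stability. Loss of benefit after IPT can also go unseen there, because week 36 is compared with a visit at which no IPT had been given. A non-significant week 12-36 result would be equally hard to read: it could mean no response, or response followed by relapse, and neither is maintenance.

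What is at stake is the interpretation of the follow-up results in the TAU arm. The trial's main effectiveness conclusion is not at stake.

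**Working it through.** **Step 1: place the contrasts on the treatment timeline.** The inputs are 12 weekly sessions, visits at weeks 0, 12, 24 and 36, and IPT offered to TAU women after the week-12 visit. The TAU column assumes a prompt start and completion by week 24, which the article does not fix.

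| | IPT + TAU | TAU |
|---|---|---|
| IPT period | weeks 0-12 | about weeks 12-24 |
| Week 12 is | end of IPT | before IPT |
| Week 24 is | 24 - 12 = 12 weeks after IPT | 24 - 24 = 0 weeks after IPT |
| Week 36 is | 36 - 12 = 24 weeks after IPT | 36 - 24 = 12 weeks after IPT |
| Planned 12-24 contrast | maintenance | response to IPT, no control |
| Planned 12-36 contrast | maintenance | response net of relapse |
| 24-36 contrast | not planned, not needed | the only post-IPT interval, not planned |

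The finding rests on this table. The article gives no figure to reproduce, and everything below is illustration under assumed rates.

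**Step 2: numbers available in the TAU arm.** Take 100 women per arm (200 in total, equal allocation assumed) and read the Sample size section's 20% attrition as applying at each follow-up visit. That leaves 100 × 0.8² = 64 at week 24 and 100 × 0.8³ ≈ 51 at week 36.

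**Step 3: one assumed course.** Let the TAU-arm diagnosis rates be 60%, 35% and 50% at weeks 12, 24 and 36. The change after IPT is 50 - 35 = +15 points (relapse). The planned week 12-36 contrast sees 50 - 60 = -10 points (improvement).

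- Week 12-24, 25-point fall, 30% remitting and 5% newly positive: exact McNemar power is 0.86 with 51 women, 0.94 with 64 and 0.99 with 100.
- Week 12-36, 10-point fall, 51 women: exact McNemar power is 0.12 with discordant proportions of 30% and 20%, 0.18 with 20% and 10%, and 0.25 with 15% and 5%.

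Under this course the first planned test usually shows a significant change. The second is usually non-significant. Neither shows the relapse.

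**Step 4: a range of courses.** Assume 51 or 100 women, week-12 MDD of 60% or 80%, remission on IPT of 50% or 70%, relapse among remitters of 20%, 40% or 50%, and no other changes of status. With all discordant pairs in one direction, the two-sided exact McNemar p-value is 2 × 0.5^b for b discordant pairs.

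- 100 women, 80% MDD, 70% remission, 40% relapse: 80 cases at week 12, 80 - 56 = 24 at week 24, and 24 + 22 = 46 at week 36. Week 12-24: 2 × 0.5^56 ≈ 3e-17. Week 12-36: b = 56 - 22 = 34, so p ≈ 1e-10. Both point to improvement. Week 24-36: b = 22, so p ≈ 5e-7, towards relapse.
- Across all 24 combinations, both planned contrasts were significant as improvement. The largest p was 2 × 0.5^8 = 0.008, in a case where half of the remitters had relapsed. The unplanned week 24-36 contrast ranged from p = 0.25 (3 relapses) to below 1e-8.

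Steps 3 and 4 differ because step 4 allows no woman to become newly positive other than by relapse. The planned week 12-36 result in the TAU arm can therefore range from clear improvement to a null finding, depending on the rates assumed.

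**The case against.** **The flaw is in a secondary analysis.** This stands. TAU women complete the week-12 assessment before IPT is offered, so the primary comparison is untouched. The IPT + TAU contrasts are valid maintenance contrasts.

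**Relapse after IPT is examined in this trial.** This also stands. A reader might infer from the TAU problem that the trial never tests relapse. The article does not support that, because the IPT + TAU arm is followed from the end of IPT to weeks 24 and 36. The gap is in the TAU arm only.

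**The arms are not compared at week 36.** Correct. A reader might infer that week-36 results 24 and about 12 weeks after IPT will be compared as equal follow-up. The article plans only within-arm tests there.

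**IPT is offered, with no fixed start or finish.** This stands as a limit on the remedy. Late starts or refusals would mean that week 24 is not the end of IPT for every TAU woman. They do not turn week 12 into a post-IPT visit.

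**The wording might be meant for the IPT + TAU arm, for gains made on TAU alone, or to include week 24 against week 36.** The text does not support these readings. It names each condition and starts both contrasts at week 12. Gains made on TAU alone cannot be followed once IPT is offered.

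**The illustration is hypothetical.** Agreed. In particular, a claim that relapse would always appear as significant improvement is too strong, as step 3 shows.

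**Conclusion.** The stated rule is wrong as written for the TAU arm and should be fixed. It labels uncontrolled response to deferred IPT (weeks 12-24) and response net of relapse (weeks 12-36) as maintenance, and it omits the interval that could show maintenance in that arm. Both planned contrasts in one of two arms are affected, about half of the randomised women if allocation is equal. The error follows from the visit schedule and the timing of IPT, and needs no assumed rate. Only the description of weeks 12-24 as the TAU arm's IPT period rests on an assumption, namely prompt start and completion of the 12 sessions. The numerical size of any distortion is unknown, since the article gives no diagnosis rates for these visits. The main effectiveness result and the IPT + TAU maintenance results stand.

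**What to change.** Reword the maintenance sentence in the Effectiveness analysis, or settle it in the analysis plan, so that the reference visit is the end of IPT in each arm:

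- IPT + TAU arm: keep weeks 12-24 and 12-36.
- TAU arm: test weeks 24-36 among women who started deferred IPT and completed it by week 24. State that condition, and report how many women fall outside it.
- TAU arm, weeks 12-24: report separately as uncontrolled pre-post response to deferred IPT.
- Label all follow-up results by weeks since the end of IPT. As a caution for reporting, week 36 is then about 24 weeks after IPT in one arm and about 12 in the other.

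If diagnosis rates are used to illustrate the issue, show them as an assumed range.

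The cost is small. The same instruments are already planned at all four visits in both arms, so no visit or measurement is added; the completion date of deferred IPT must be available for each TAU woman. The downside is that the TAU arm contributes one maintenance interval of about 12 weeks in place of two contrasts, in a self-selected subset with fewer women.

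### The week 24 and 36 tests leave out the therapist clustering that the plan models in its main analysis, so p-values may be too small, chiefly in the TAU arm

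*Protocol article*

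**What the plan says.** The Effectiveness part of the protocol's Statistical analysis section sets out two analyses.

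- **Main analysis, baseline to week 12.** MDD and PTSD diagnosis are modelled with a binomial distribution and log link. Generalized estimating equations (GEE) are used to "account for clustering of participants by therapist (therapist effect) and the repeated assessments".
- **Follow-up.** Maintenance of gains is judged by "testing for significant change from 12-week to 24- and 36-week follow-up assessments", and this is done "within each condition using McNemar’s test and repeated measures" t tests. No therapist term is mentioned.

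Two other sections bear on who is being treated during follow-up. Study design states: "The TAU group will be offered IPT treatment following the initial 12-week trial". It adds that "they will all receive IPT in either the first or second half of the study". Treatment as usual repeats the point: "Thus, all study subjects will receive IPT during the course of the study".

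The protocol gives no number of therapists, no ICC, and no power or precision figure for the follow-up tests.

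**The concern.** McNemar's test and the paired t test deal with the correlation between two measurements on the same woman. Both assume that one woman's change is independent of another's. The plan has already accepted that this may fail for women who share a therapist, because it models a therapist effect at week 12.

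The term is dropped in the period when more women are due to be in therapy. Up to week 12 only the IPT + TAU arm has IPT therapists. After week 12 the TAU arm is offered the same 12 weekly sessions, so its change from week 12 to week 24 is planned to span a full course of IPT. That is the kind of response for which the plan wants a therapist effect in the other arm.

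If women with the same therapist improve to a similar degree, the naive standard error of the arm's mean change is too small. Significant change would then be declared more often than the nominal 5%.

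**Working it through.** **The plan's own figure.** There is none for these tests. The only design calculation, in Sample size, concerns the two-group comparison and plays no part here. The sole input taken from it is the 0.05 level ("power of 50 and probability level of 0.05"), read as two-sided because the sidedness is not stated.

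**Inputs**

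| Input | Value | Source |
|---|---|---|
| Women randomized | 200 | Sample size (Randomization gives 220) |
| Women per arm | 100 | assumed 1:1 allocation |
| Loss per assessment | about 20% | Sample size |
| Left per arm, week 24 | 100 × 0.8² = 64 | arithmetic |
| Left per arm, week 36 | 100 × 0.8³ = 51.2 | arithmetic |
| Therapists per arm, k | 6 or 10 | assumed |
| ICC of change | 0.01, 0.05, 0.10 | assumed |

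**Formulas.** With m = n/k women per therapist, the design effect is DE = 1 + (m − 1) × ICC. The true standard error is √DE times the naive one. The actual error of a nominal 5% test is 2 × [1 − Φ(1.96/√DE)].

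**Worked case: week 24, 6 therapists, ICC 0.05.** m = 64/6 = 10.67. DE = 1 + 9.67 × 0.05 = 1.48 and √DE = 1.22. The actual error is 2 × [1 − Φ(1.96/1.218)] = 10.8%.

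**Actual error of a nominal 5% test**

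| Visit | k | m | ICC 0.01 | ICC 0.05 | ICC 0.10 |
|---|---|---|---|---|---|
| Week 24 | 6 | 10.67 | 6.1% | 10.8% | 16.2% |
| Week 24 | 10 | 6.40 | 5.6% | 8.2% | 11.4% |
| Week 36 | 6 | 8.53 | 5.9% | 9.5% | 13.9% |
| Week 36 | 10 | 5.12 | 5.5% | 7.4% | 9.9% |

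At ICC 0.05 the true standard error is 1.13 to 1.22 times the naive one at week 24, and 1.10 to 1.17 times at week 36.

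**Simulation check.** Each setting used 10,000 simulated arms with 10 therapists. The entries are rejection rates when there is no true mean change.

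| Therapist effect | Women | ICC | Paired t | McNemar |
|---|---|---|---|---|
| In the change only | 100 | 0.05 | 10.3% | 7.9% |
| In the change only | 100 | 0.10 | 15.8% | 10.4% |
| In the change only | 60 | 0.05 | 7.7% | 6.2% |
| In the change only | 60 | 0.10 | 10.5% | 8.0% |
| Same at both visits | 60 or 100 | 0.05 or 0.10 | 4.9–5.3% | 4.8–5.5% |

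The simulation shows three things.

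1. The formula describes the paired t test well. For 100 women and 10 therapists it gives 10.4% and 15.5%, against 10.3% and 15.8% simulated.
2. McNemar's test, which suits the two diagnoses, is inflated less than the formula says.
3. A therapist effect of equal size at both visits cancels in the change and does no harm.

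The third result separates the arms. A woman in the TAU arm has no IPT therapist at week 12, so her therapist effect arises between the two visits and cannot cancel. A woman in the IPT-first arm has completed her course by week 12. Only therapist differences that grow or fade afterwards would remain in her change.

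**The case against.** The strongest reply is that these tests use within-woman change, so pairing already removes stable therapist differences. In the IPT-first arm this largely stands. Therapy has ended, and nothing in the protocol shows that later change clusters by therapist. In the TAU arm it does not stand, for the reason just given.

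Other points also carry weight.

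- **Size is unknown.** Therapists must score consistently high on a pilot case before treating trial participants, and they have weekly expert supervision. Both are meant to limit therapist differences, so the low end of the ICC range is plausible.
- **The estimate is not biased.** Averaged over therapists, the arm's mean change is unaffected. Only its uncertainty is understated, for inference beyond the therapists in the trial.
- **Uptake may be incomplete.** IPT is offered to TAU women, and those who decline add no therapist clustering.
- **The analysis is secondary**, and the article is condensed. That does not excuse the omission, because the article names the tests outright.

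A reader might infer that the follow-up p-values are certainly too small in both arms, and in a direction that flatters IPT. The documents do not support this. Inflation depends on an ICC of change that is not given. In the IPT-first arm, maintenance is presumably read from the absence of significant worsening, so p-values that are too small would suggest false relapse and count against IPT. A reader might also infer that reported intervals are too narrow, but the plan names only significance tests for this analysis.

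**Conclusion.** The inconsistency is real and limited. The plan requires therapist clustering in its main model and omits it from the week 24 and 36 tests. The omission bears mainly on the TAU arm's changes from week 12 to weeks 24 and 36.

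At an ICC of change of 0.05, with 1:1 allocation and 6 to 10 therapists per arm, the actual error of a nominal 5% test is about 8–11% at week 24 and about 7–9.5% at week 36. It is somewhat less for McNemar's test and close to 5% if the ICC is near 0. Allocation, therapist numbers and ICC are all assumptions, so these figures show what could happen and do not predict it. The primary week 12 comparison between arms is untouched. This is a cheap improvement to a secondary analysis.

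**What to change.** Replace McNemar's test and the paired t tests with contrasts from the GEE that the plan already names, extended to weeks 24 and 36:

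- Estimate the week 12 to 24 and week 12 to 36 contrasts within each arm, for the two diagnoses and, with a suitable distribution and link, for the symptom scores.
- Cluster on the woman's IPT therapist, and treat each woman who does not take up IPT as her own cluster.
- Apply a small-sample variance correction, and base the reference distribution on the number of therapists, since single-woman clusters would otherwise make the cluster count look larger than it is.
- Report each change with its interval.

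The cost is modest. Each woman's therapist must be recorded, intervals become somewhat wider, and the small-sample correction is an addition to what the plan names. GEE with few therapists is itself fragile, so the correction and the handling of decliners should be fixed before the follow-up data are analysed. If change turns out not to cluster by therapist, the estimates should differ little from the paired tests.
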